### **Demographics**

At Visit 1, each subject shall be required to provide demographic information (including date of birth, height, weight, gender, and race).

### **ELISA for anti-malarial antibodies**

During pre-screening period (D-21 through D-15), a blood sample will be collected for assessment of anti-malarial antibody titres by ELISA. Subjects without evidence of IgG antibodies against PfMSP-119 and PfF2 as measured by ELISA will be further administered the main informed consent.

### **Medical History**

At Visit 2, all subjects will be questioned regarding current signs and symptoms, their active and past medical history and other relevant chronic medical conditions and the same will be recorded as a part of medical history.

### **Concomitant Medications**

A concomitant medications history will be sought at every visit including screening visit (at any time in the screening period of D-14 through D-1 and those subjects who have medicated themselves with any of the prohibited medications during the study period may be terminated from the study.

### **Physical Examination/Vital Signs/12-lead ECG**

A general physical examination including vital signs (temperature, pulse rate, respiratory rate and blood pressure) will be performed at each visit. 12-lead ECG will be done only once at any time in the screening period of D-14 through D-1. Vital signs will be recorded after the subject has been resting quietly for at least five (5) minutes. BP will be recorded in the supine position.

### **Birth Control Counselling**

All male subjects participating in the study will be counselled at the pre-defined visits (including screening visit) regarding the various birth control options described in the protocol. The importance of strict adherence to the birth control measures in order to avoid pregnancy in the female partner during the study duration will be emphasised.

### **Haematology**

Blood samples will be collected on Days -14, 28, 56, 180, 208 and 365 for haematology assessments like RBC Count, Haemoglobin\*, Haematocrit/Packed Cell Volume (PCV), MCV

*Information contained in this publication is the property of EVI and ICGEB and is confidential and will not be disclosed to third parties without written authorization from EVI and ICGEB. No part of this document may be reproduced, stored in a retrieval system or transmitted in any form or by any means -electronic, mechanical, recording or otherwise - without the prior authorization of EVI and ICGEB*

[figure not shown][figure not shown]

(Mean Corpuscular Volume), MCH (Mean Corpuscular Haemoglobin), MCHC (Mean Corpuscular Haemoglobin Concentration), Platelet Count and Total Leukocyte Count (TLC) along with Differential Leukocyte Count (DLC). *\*If the haemoglobin drops below 13 gm/dL, then a direct Coomb's test and a peripheral blood smear/film will be prepared and examined for evidence of possible haemolysis*

### **Serum Chemistry**

Blood samples will be collected on Days -14, 28, 56, 180, 208 and 365 for serum chemistry assessments which include potassium, sodium, AST, ALT, direct, indirect and total bilirubin, alkaline phosphatase,  $\gamma$ GT, creatinine and random blood glucose. At the discretion of the Investigator, additional laboratory testing maybe performed to assist in identifying any other conditions that may affect the subject's eligibility.

### **HIV, HBV and HCV Tests**

Blood samples will be collected at Visit 2 for HIV, HBV and HCV testing. Those who test positive will not be included in the study and appropriately counselled and managed as per applicable policies.

### **Direct Coombs Test and Peripheral Blood Smear**

Test for Direct Coomb's test and peripheral blood smear/film for evidence of haemolysis will be done at screening and subsequently when haemoglobin drops to less than 13 gm/dL

### **Urine Drug Screen**

Urinalysis to test for drugs of abuse (benzodiazepines, opioids, amphetamine, cocaine, and THC) will be undertaken at Visits 2, 6, 10 and 14

### **Randomisation Number**

A subject will be randomised into the study and assigned a unique randomisation number only after completion of an eligibility check of a subject's inclusion/exclusion criteria by the Investigator. The subject will be recognised by the randomisation number for all study-related assessments and procedures.

### **Diary Cards**

Distribution: Pre-printed diary cards will be given to subject on the days of vaccine administration (Days 0, 28 and 180) and will be collected on Day 28 following each vaccination. Detailed instructions to fill the diary cards will be given to the subjects at the time of dispensing the diary. These diary cards will be used for the record of solicited AEs (local and systemic reactogenicity) till Day 14 and unsolicited AEs till Day 28 after each vaccination by the subject. Thus three (3) such diary cards will be given to each subject.

Review and Transcription: 7 and 14 days after each vaccination, i.e. on Days 7, 14, 35, 42, 187 and 194, the investigator will review the subject diary card and transcribe the local and systemic reactogenicity data and the unsolicited AEs from the subject diary cards into the CRF.

Collection: Pre-printed diary cards given to the subject on the days of vaccine administration (Days 0, 28 and 180) will be collected 28 days after each vaccination i.e. respectively on Days 28, 56 and 208.

### **Record Immediate Reactogenicity**

*Information contained in this publication is the property of EVI and ICGEB and is confidential and will not be disclosed to third parties without written authorization from EVI and ICGEB. No part of this document may be reproduced, stored in a retrieval system or transmitted in any form or by any means -electronic, mechanical, recording or otherwise - without the prior authorization of EVI and ICGEB*

[figure not shown][figure not shown]

On Day 0, 28 and 180, after administration of the assigned study vaccine, the subject will be monitored for any changes in vital signs (including temperature, pulse, respiratory rate and blood pressure) every 30 minutes till 3 hours post-vaccination. Appropriate medical treatment will be readily available at the study site to manage any adverse event with special emphasis on allergic/anaphylactic reactions. Vital signs will be assessed after the subject has been resting quietly for at least five (5) minutes. BP will be taken in the supine position.

#### **Record Solicited AEs (Local and Systemic Reactogenicity)**

Subjects will record solicited AEs for 14 days following each vaccination. The investigator will transcribe the solicited AEs data from the diary cards into the CRF on Days 7, 14, 35, 42, 187 and 194. All solicited AEs will also be independently assessed by the investigator 14 days after each vaccination (Days 14, 42 and 194).

#### **Record Unsolicited AEs and SAEs**

Subjects will record unsolicited AEs for 28 days following each vaccination in the diary cards. The Investigator will report all unsolicited adverse events that occur during the first 28 days following each dose of the vaccine and all SAEs during the entire study period (from study inclusion till last follow-up visit i.e. Day 365)

#### **Serology Assessments**

Blood samples will be collected on Days 0, 28, 56, 180, 208 and 365 for assessment of:

- IgG antibodies developed against PfMSP-119 and PfF2 by ELISA
- Ability of the IgG antibodies developed against PfMSP-119 and PfF2 to recognise the native protein on late stage *P. falciparum* schizonts and merozoites *in vitro* by IFA
- IgG1, IgG2, IgG3, IgG4 subclasses by ELISA

Blood samples will be collected on Days 0, 56, 208 and 365 for assessment of ability to block parasite growth *in vitro* by a *P. falciparum* blood-stage growth inhibition assay (GIA) against three (3) parasite strains

#### **Check Discontinuation Criteria**

At Visits 4, 5, 6, 7, 8, 9, 10, 11, 12 and 13 the Investigator will check for development of the subject discontinuation criteria per section 5.4.4.

### **7.4.3 Visit-wise Study Procedures and Assessments**

#### **7.4.3.1 Visit 1 (Day -21 to Day -15), Pre-Screening Visit**

- Pre-Screening Informed consent
- Assignment of screening number
- Demographics
- ELISA for anti-malarial antibodies

#### **7.4.3.2 Visit 2 (Day -14 to Day -1), Screening Visit**

- Main Informed consent

*Information contained in this publication is the property of EVI and ICGEB and is confidential and will not be disclosed to third parties without written authorization from EVI and ICGEB. No part of this document may be reproduced, stored in a retrieval system or transmitted in any form or by any means -electronic, mechanical, recording or otherwise - without the prior authorization of EVI and ICGEB*

[figure not shown][figure not shown]

- Medical history/concomitant medications
- Physical examination/vital signs/12-lead ECG
- Birth control counselling
- Haematology (*direct Coomb's test and peripheral blood smear*)
- Serum chemistry
- HIV, HBV, HCV tests
- Urine drug screening for drugs of abuse
- Check inclusion criteria
- Check exclusion criteria

#### **7.4.3.3 Visit 3 (Day 0, First Dose of the Vaccine)**

- Concomitant medications
- Physical examination/vital signs
- Birth control counselling
- Check inclusion criteria
- Check exclusion criteria
- Assignment of randomisation number
- Distribution of first diary card by Investigator
- Vaccine administration (first dose)
- Record of immediate reactogenicity (first dose)
- Record of solicited and unsolicited AEs/SAEs by subject in diary card
- Serology (ELISA, IFA, IgG subclasses and GIA)

#### **7.4.3.4 Visit 4 (Day 7)**

- Concomitant medications
- Physical examination/vital signs
- Review of first diary card by Investigator
- Transcription of data from diary card to CRF by Investigator (solicited and unsolicited AEs)
- Record of any SAEs by Investigator
- Check discontinuation criteria

#### **7.4.3.5 Visit 5 (Day 14)**

- Concomitant medications

*Information contained in this publication is the property of EVI and ICGEB and is confidential and will not be disclosed to third parties without written authorization from EVI and ICGEB. No part of this document may be reproduced, stored in a retrieval system or transmitted in any form or by any means -electronic, mechanical, recording or otherwise - without the prior authorization of EVI and ICGEB*

[figure not shown][figure not shown]

- Physical examination/vital signs
- Review of first diary card by Investigator
- Transcription of data from diary card to CRF by Investigator (solicited and unsolicited AEs)
- Independent assessment by Investigator and direct record in CRF (solicited and unsolicited AEs)
- Record of any SAEs by Investigator
- Check discontinuation criteria

#### **7.4.3.6 Visit 6 (Day 28, Second Dose of the Vaccine)**

- Concomitant medications
- Physical examination/vital signs
- Birth control counselling
- Haematology (*direct Coomb's test and peripheral blood smear if required*)
- Serum chemistry
- Urine drug screening for drugs of abuse
- Collection and review of first diary card by Investigator (unsolicited AEs)
- Transcription of data from diary card to CRF by Investigator (unsolicited AEs)
- Distribution of second diary card by Investigator
- Vaccine administration (second dose)
- Record of immediate reactogenicity (second dose)
- Record of any SAEs by Investigator
- Serology (ELISA, IFA and IgG subclasses)
- Check discontinuation criteria

#### **7.4.3.7 Visit 7 (Day 35)**

- Concomitant medications
- Physical examination/vital signs
- Review of second diary card by Investigator
- Transcription of data from diary card to CRF by Investigator (solicited and unsolicited AEs)
- Record of any SAEs by Investigator
- Check discontinuation criteria

*Information contained in this publication is the property of EVI and ICGEB and is confidential and will not be disclosed to third parties without written authorization from EVI and ICGEB. No part of this document may be reproduced, stored in a retrieval system or transmitted in any form or by any means -electronic, mechanical, recording or otherwise - without the prior authorization of EVI and ICGEB*

[figure not shown][figure not shown]

#### **7.4.3.8 Visit 8 (Day 42)**

- Concomitant medications
- Physical examination/vital signs
- Review of second diary card by Investigator for second dose (solicited and unsolicited AEs)
- Transcription of data from diary cards to CRF by Investigator for second dose (solicited and unsolicited AEs)
- Independent assessment by Investigator and direct record in CRF for second dose (solicited and unsolicited AEs)
- Record of any SAEs by Investigator
- Check discontinuation criteria

#### **7.4.3.9 Visit 9 (Day 56)**

- Concomitant medications
- Physical examination/vital signs
- Haematology (*direct Coomb's test and peripheral blood smear if required*)
- Serum Chemistry
- Collection and review of second diary card by Investigator (unsolicited AEs)
- Transcription of data from diary card to CRF by Investigator (unsolicited AEs)
- Record of any SAEs by Investigator
- Serology (ELISA, IFA, IgG subclasses and GIA)
- Check discontinuation criteria

#### **7.4.3.10 Visit 10 (Day 180, Third Dose of the Vaccine)**

- Concomitant medications
- Physical examination/vital signs
- Birth control counselling
- Haematology (*direct Coomb's test and peripheral blood smear if required*)
- Serum chemistry
- Urine drug screening for drugs of abuse
- Distribution of third diary card by Investigator
- Vaccine administration (third dose)
- Record of immediate reactogenicity (third dose)
- Record of any SAEs by Investigator

*Information contained in this publication is the property of EVI and ICGEB and is confidential and will not be disclosed to third parties without written authorization from EVI and ICGEB. No part of this document may be reproduced, stored in a retrieval system or transmitted in any form or by any means -electronic, mechanical, recording or otherwise - without the prior authorization of EVI and ICGEB*

[figure not shown][figure not shown]

- Serology (ELISA, IFA and IgG subclasses)
- Check discontinuation criteria

#### **7.4.3.11 Visit 11 (Day 187)**

- Concomitant medications
- Physical examination/vital signs
- Review of third diary card by Investigator
- Transcription of data from diary card to CRF by Investigator (solicited and unsolicited AEs)
- Record of any SAEs by Investigator
- Check discontinuation criteria

#### **7.4.3.12 Visit 12 (Day 194)**

- Concomitant medications
- Physical examination/vital signs
- Review of third diary card by Investigator for third dose (solicited and unsolicited AEs)
- Transcription of data from diary cards to CRF by Investigator for third dose (solicited and unsolicited AEs)
- Independent assessment by Investigator and direct record in CRF for third dose (solicited and unsolicited AEs)
- Record of any SAEs by Investigator
- Check discontinuation criteria

#### **7.4.3.13 Visit 13 (Day 208)**

- Concomitant medications
- Physical examination/vital signs
- Collection and review of third diary card by Investigator (unsolicited AEs)
- Transcription of data from diary card to CRF by Investigator (unsolicited AEs)
- Haematology (*Direct Coomb's test and peripheral blood smear if required*)
- Serum chemistry
- Record of any SAEs by Investigator
- Serology (ELISA, IFA, IgG subclasses and GIA)
- Check discontinuation criteria

#### **7.4.3.14 Visit 14 (Day 365, End of Study Visit)**

- Concomitant medications

*Information contained in this publication is the property of EVI and ICGEB and is confidential and will not be disclosed to third parties without written authorization from EVI and ICGEB. No part of this document may be reproduced, stored in a retrieval system or transmitted in any form or by any means -electronic, mechanical, recording or otherwise - without the prior authorization of EVI and ICGEB*

[figure not shown][figure not shown]

- Physical examination/vital signs
- Haematology (*direct Coomb's test and peripheral blood smear if required*)
- Serum chemistry
- Urine drug screening for drugs of abuse
- Record any SAEs by the Investigator
- Serology (ELISA, IFA, IgG subclasses and GIA)

*Information contained in this publication is the property of EVI and ICGEB and is confidential and will not be disclosed to third parties without written authorization from EVI and ICGEB. No part of this document may be reproduced, stored in a retrieval system or transmitted in any form or by any means -electronic, mechanical, recording or otherwise - without the prior authorization of EVI and ICGEB*

[figure not shown][figure not shown]

## 8 SAFETY MONITORING

### 8.1 Introduction

The collection, recording, assessment and reporting of adverse events (AE) and serious adverse events (SAE) represent the core activities for the safety evaluation. These activities are under the direct responsibility of the Investigator.

The recording of adverse events is an important aspect of study documentation as the evaluation of the safety of three (3) intramuscular injections of the investigational vaccine (JAIVAC-1 – Montanide ISA 720 malaria vaccine) in comparison with that of the control vaccine (Hepatitis B vaccine) is the primary objective of this study. The procedure for evaluation of immediate reactogenicity, solicited adverse events and unsolicited adverse events is described Section 7. The investigator is responsible for the detection and documentation of events meeting the definition of an adverse event (AE) or a serious adverse event (SAE) as provided in Sections 8.4 and 8.5 of this protocol. This includes the evaluation of its seriousness, its severity, and the causal relationship to the investigational vaccine and/or concomitant therapy.

At each visit, the investigator will assess whether any AE including laboratory abnormalities has occurred. The investigator shall inquire for unsolicited AEs with non-suggestive questions to the subject at each study visit. The investigator shall attempt to establish a diagnosis of the event based on signs, symptoms and/or other clinical information. The diagnosis shall be recorded as the AE and/or SAE and not the individual symptoms.

If a laboratory abnormality or other abnormal assessment meets the definition of an AE or SAE, the Adverse Event or Serious Adverse Event Form shall be completed as appropriate. A diagnosis, if known or clinical signs and symptoms if diagnosis is unknown, rather than the laboratory abnormality shall be reported. If no diagnosis is known and clinical signs and symptoms are not present, then the abnormal finding shall be recorded. The subject shall be observed and monitored carefully until the AE resolves, the condition stabilises or its cause is identified completely. The investigator is responsible for ensuring that follow-up includes any supplemental investigations that may be indicated to elucidate the nature and/or the cause of the event.

### 8.2 Data Safety Monitoring Board

An independent Data Safety Monitoring Board (DSMB) will be set up prior to initiating the study comprising of three (3) independent clinicians with relevant expertise in the field of vaccines development and evaluation of vaccine safety along with the designated Local Safety Monitor (who would be a designated personnel from the investigational site but independent of the study team). Dose escalation to the next higher dosage cohort of JAIVAC-1 – Montanide ISA 720 will occur after the safety data from the first dose of vaccine through Day 14 day for all 15 subjects of the previous dosage cohort has been reviewed by the DSMB.

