#### FOOTNOTES:

The defined study period for the JAIVAC-1\_1\_09 study consists of four (4) distinct study periods; a pre-screening period of seven (7) days, a screening period of 14 days, a vaccination period of 180 days and a follow-up period till 365 days from the first dose of the assigned study vaccine.

Each cohort will consist of 15 subjects. Dosing of the JAIVAC-1 – Montanide ISA 720 investigational vaccine arms will begin with Cohort 1 (10µg PfMSP-119 + 10µg PfF2 i.e. Dosage A), followed by Cohort 2 (25µg PfMSP-119 + 25µg PfF2 i.e. Dosage B) and finally Cohort 3 (50µg PfMSP-119 + 50µg PfF2 i.e. Dosage C) as per the common vaccine administration schedule (administered as a 3-dose schedule on Days 0, 28 and 180 by intramuscular route) at each dosage. Each cohort will be staggered into sub-cohorts such that the subjects in each cohort will be enrolled over a three-day period. The first three (3) subjects of the first dose (Cohort 1) will be kept under observation for 24 hrs following vaccination. The decision of the 24-hour housing for the remaining subjects will be jointly taken by the Principal Investigator and Medical and Safety Monitor, DLS.

Dose escalation to the next higher dosage cohort of JAIVAC-1 – Montanide ISA 720 will occur after review of the appropriately monitored and verified safety data obtained from the first dose of the vaccine through Day 14 for all 15 subjects in the previous dosage cohort. The “Safety Review” will be undertaken by the DSMB comprising of three (3) independent clinicians with relevant expertise along with the designated Local Safety Monitor (who would be a designated personnel from the investigational site but independent of the study team). The decision to begin the next cohort will be taken in the next 7 days. Thus, the next dosage cohort may begin at the earliest at 21 days after the 15th subject enrolled in the given dosage cohort has been administered the first dose of the JAIVAC-1 – Montanide ISA 720.

Information contained in this publication is the property of EVI and ICGEB and is confidential and will not be disclosed to third parties without written authorization from EVI and ICGEB. No part of this document may be reproduced, stored in a retrieval system or transmitted in any form or by any means -electronic, mechanical, recording or otherwise - without the prior authorization of EVI and ICGEB

[figure not shown][figure not shown]

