## 9.6 Study and Site Closure

Premature termination of the clinical trial may occur because of a regulatory authority decision, change in the opinion of the IEC/IRB or vaccine safety issues at the discretion of EVI/ICGEB. Recruitment at a centre may be stopped for reasons of particularly low enrolment, protocol violations, or inadequate data recording. The investigator also must provide follow-up medical care for all subjects who are prematurely withdrawn from the study, or must refer them for appropriate ongoing care. Once the study ends formally at the site either because the study has been completed (all the subjects have completed their participation in the study) or because of other reasons such as poor enrolment rates, poor site performance or IEC/IRB decision, investigator /site/ decision etc, the following close out activities will be done:

- “End of Study” letter will be sent to the investigator
- Instructions for retention of study documents at the site will be given to the investigators
- Unused CRF's, non vaccine supplies and equipment should be returned to EVI/ICGEB or designee or destroyed at site as per instructions provided by the sponsor.
- All study vaccines should be accounted for and the unused supplies returned to EVI/ICGEB or designee or destroyed at the site as per instructions.
- Investigator should send a letter to the IEC/IRB stating that the study has been closed.
- The study monitor will further guide the investigators regarding the detailed close out activities.

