Each cohort will be staggered into sub-cohorts such that the subjects in each cohort will be enrolled over a three-day period. The first three (3) subjects of the first dose (Cohort 1) will be kept under observation for 24 hrs following vaccination. Dose escalation to a higher dosage of JAIVAC-1 – Montanide ISA 720 will occur after review of safety data by the DSMB through Day 14 after the first vaccination for all subjects in a cohort. In each cohort, each subject will receive a total of three (3) doses of either of the study or control vaccines by intramuscular route, one each on Day 0, Day 28 and Day 180 respectively.

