## 11.2 Timing of Analysis

The data collected will be analysed at the end of the study i.e. after the last subject/last visit has been completed and the data has been locked. An interim analysis will be undertaken for data obtained till 28 days after the third dose of the vaccine for each dose-level (cohort). The details of the same will be stated in the SAP.

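### The DSMB's only stated task is a first-dose, Day 14 review before the next cohort opens; no stated review covers second- or third-dose data, or any data from the highest-dosage cohort

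*Supplement*

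**What the plan says.** Section 8.2 sets up an independent DSMB of three clinicians plus a Local Safety Monitor. Escalation follows once it has reviewed "safety data from the first dose of vaccine through Day 14 day for all 15 subjects of the previous dosage cohort". Section 11.1.2 makes escalation follow "review of safety data by the DSMB through Day 14 after the first vaccination for all subjects in a cohort". The Synopsis (Study Design), the study design footnotes there and in Section 4.1, and Sections 4.2 and 7.1 give the same task. Section 4.2 does not name the first dose; the others do.

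On timing, the design footnotes say "The decision to begin the next cohort will be taken in the next 7 days", so that "the next dosage cohort may begin at the earliest at 21 days after" the 15th subject's first dose.

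The subject of the trial is wider. Section 8.1 names "the evaluation of the safety of three (3) intramuscular injections of the investigational vaccine", compared with the control vaccine, as the primary objective. The primary endpoints in Section 4.6.1 cover reactions, unsolicited events and laboratory safety after each vaccination.

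Section 11.2 plans an interim analysis per cohort on data to 28 days after the third dose. It names no DSMB recipient. Section 8.5.3 sends SAE reports to the sponsor, the ethics committee, the institutional review board and the DCGI; the DSMB is not listed. Section 9.6 allows early termination by the regulator, by a change in the ethics committee's opinion, or for "vaccine safety issues at the discretion of EVI/ICGEB". Section 5.5 is similar. Neither mentions the DSMB.

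**The concern.** The DSMB's reviews are tied to the opening of the next cohort, and this has two consequences. Data after the second and third injections never trigger a review in any cohort. Cohort 3, at the highest dosage, has no cohort after it, so nothing triggers a review of its data even after the first injection.

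Reactions that appear or worsen on repeat injection are part of what this trial is meant to find. The repeat-dose animal studies in Section 2.4 reported local inflammatory reaction at the injection site, and the investigator looks for injection-site nodules on Days 14, 42 and 194 (Section 7.2.2.2). Investigators, assessors and analysts are unblinded (Section 4.5), which adds to the value of an independent reading. The Day 42 and Day 194 data are collected, but no text assigns them to the DSMB.

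**Working it through.** **Inputs.** 30 JAIVAC-1 subjects, 10 per cohort, and 15 controls, 5 per cohort (Section 5.3). Doses on Days 0, 28 and 180. Visits on Days 14, 42, 56, 194 and 208, with windows of ±1 day (Table 1). Enrolment of each cohort over three days, so the last subject starts 2 days after the first (3 days as a sensitivity). Decision time of 7 days (design footnotes).

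**The plan's own figure.** 14 days of follow-up + 7 days to decide = 21 days. The stated earliest start of the next cohort is reproduced.

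**Coverage of the stated reviews.**
- JAIVAC-1: 30 × 3 = 90 injections. Reviewed: 10 + 10 = 20 (22%). Not reviewed: 70 (78%).
- With controls: 45 × 3 = 135 injections. Reviewed: 15 + 15 = 30. Not reviewed: 105 (78%).
- Cohort 3 JAIVAC-1: 0 of 30.

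**Does a review of a cohort's own data fit before its next dose?** Count from the cohort's first injection. Review complete = last subject's offset + visit day + 7. Time to spare = day of the first next dose − review complete. The adverse case puts the data visit one day late and the dose one day early, which removes 2 days.

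| Review | Offset | Review complete | Next dose | To spare | Adverse windows |
|---|---|---|---|---|---|
| Day 14 data | 2 days | 2 + 14 + 7 = 23 | 28 | 5 | 3 |
| Day 14 data | 3 days | 3 + 14 + 7 = 24 | 28 | 4 | 2 |
| Day 42 data | 2 days | 2 + 42 + 7 = 51 | 180 | 129 | 127 |
| Day 42 data | 3 days | 3 + 42 + 7 = 52 | 180 | 128 | 126 |
| Day 56 laboratory data | 2 days | 2 + 56 + 7 = 65 | 180 | 115 | 113 |
| Day 56 laboratory data | 3 days | 3 + 56 + 7 = 66 | 180 | 114 | 112 |

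The result is the same in every cohort. On the earliest study calendar with a 2-day offset, first doses fall on study days 0–2, 23–25 and 46–48. Cohort 3's Day 14 review would be complete on study day 48 + 14 + 7 = 69, and its second doses start on 46 + 28 = 74.

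**Does a lower cohort's later data fit before the higher cohort's same dose?** Count from the lower cohort's last first dose, with the next cohort opening 21 days later.
- Dose 2: 21 + 28 = Day 49, against the Day 42 visit. This leaves 7 days, or 48 − 43 = 5 with adverse windows.
- Dose 3: 21 + 180 = Day 201, against the Day 194 visit. This leaves 7 days, or 200 − 195 = 5 with adverse windows.

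A 7-day decision therefore has no time to spare and does not fit in the adverse case. Nor can complete second-dose data inform escalation on the earliest calendar. Cohort 2 can open on study day 23, before Cohort 1's dose 2 on day 28. Cohort 3 can open on day 46, while a review of Cohort 1's Day 42 data would run to 2 + 42 + 7 = 51.

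**Interim analysis.** 180 + 28 = Day 208, after the cohort's last injection.

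**A limit of the Day 14 review.** The first scheduled post-vaccination safety laboratory sample is on Day 28, on the day of dose 2 (Table 1, footnotes 9 and 10). A Day 14 review therefore holds no scheduled post-vaccination laboratory results.

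**The case against.** The strongest reply is that Section 8.2 sets a condition for escalation and need not be the DSMB's whole remit. The word "only" is an inference from the absence of any other task. The SAE flowchart and design figures are not shown, some text near the SAE section is missing, and interim-analysis details are left to a SAP that is not shown. This stands as a limit on certainty. It does not remove the need to state the remit: Section 8.2 assigns nothing else, and no DSMB charter is cited in the text shown.

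A reader might infer that nobody independent sees later events, or that only the sponsors can end the trial for safety. The documents do not support that. SAE reports go to the ethics committee, the institutional review board and the DCGI (8.5.3). The regulator and the ethics committee can bring about termination (5.5, 9.6). Discontinuation criteria, which include adverse events and laboratory abnormalities, are checked at the dose 2 and dose 3 visits (5.4.4, 7.4.3.6, 7.4.3.10). These arrangements deal with serious events, individual subjects or ending the trial. None is a cohort-level independent review of local and systemic reactions before a repeat dose.

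A reader might also infer that Cohort 3 opens with no DSMB involvement. It does not: it opens after the DSMB has reviewed Cohort 2's first-dose data. In Cohorts 1 and 2 the escalation review would also end before Day 28, although no text links dose 2 to it.

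Finally, it is tempting to require the lower cohort's Day 42 and Day 194 data to be reviewed before the higher cohort's matching dose. The schedule does not support that as a required step: the 7 days available, or 5, must hold a 7-day decision, and the dosing windows are ±1 day.

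**Conclusion.** The point holds, as a should-fix. As written, DSMB review covers 20 of 90 JAIVAC-1 injections. It includes no second- or third-dose data and no Cohort 3 data, although the trial's main question is the safety of three injections. The existing visits leave room for reviews of each cohort's own data before its second dose (5 days to spare, 2 to 5 over the offsets and windows tried) and before its third dose (112 to 129 days, depending on offset, windows and whether Day 56 laboratory data are included).

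This rests on the text shown giving the DSMB's full remit, on a three-day enrolment per cohort, and on the 7-day decision time also being enough for monitoring and verifying the data. The last assumption matters most for the Day 14 review, where the margin is small.

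**What to change.** Amend Section 8.2 and its repeats (Synopsis, 4.1, 4.2, 7.1, 11.1.2), leaving dosages and visit days as they are, so that the DSMB reviews data already collected:

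1. Each cohort's own first-dose Day 14 data, including Cohort 3, timed before that cohort's Day 28 visit. For Cohorts 1 and 2 the existing escalation review can serve.
2. Each cohort's own Day 42 data, with Day 56 laboratory results if wanted, timed before its Day 180 visit.
3. The per-cohort interim analysis, with the DSMB named as a recipient in Section 11.2.

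Reviews 1 and 2 would cover 2 × 30 = 60 of 90 JAIVAC-1 injections before the subject's next dose. Item 3 would bring in the 30 third doses after the event. A lower cohort's Day 42 and Day 194 data can go to the DSMB as they become available, but should not be a required step for the higher cohort.

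Name the DSMB's advisory role in Sections 5.5 and 9.6. Any criteria for continuing, pausing or stopping are for the sponsor and the DSMB to set.

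The cost is one protocol amendment, four new short reviews (1 for Cohort 3 at Day 14 + 3 at Day 42) and circulation of three interim reports. No visits, samples or subjects are added.
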